A staff in the centre who will not involve in recruitment and the project will provide a member list to the research team. A trained research assistant (RA) will screen the member list and make sure the potential subjects will fit for the inclusion and exclusion criteria before making phone calls to them. After briefly introduce the programme to potential subjects through phone call, the RA will arrange a home visit with them to fully explain the procedure of the programme and obtain their consent forms. The RA will collect the baseline data of those who agree to participate. After successfully collecting their data, the RA will call the principal investigator (PI) of the research team for group randomisation. The subjects will be randomly assigned in a 1:1 ratio to either the intervention group or control group. Random group assignments will be generated by the PI using Research Randomizer software (i.e. 1 = intervention group; 2 = control group). These group assignments will then sealed in envelopes and opened sequentially by the PI after receiving the call from the RA. The RA and the community centre staff, but not the PI or the healthcare providers, will be blinded to the group assignments. The PI will neither involve in recruitment process nor data collection. To prevent contamination between the intervention and control groups within the centre, strategies such as clearly communicate the procedures and interventions specific to each group and provide ongoing reminders throughout the study, maintain confidentiality regarding group assignments, and implement regular monitoring and supervision of the study activities will be adopted.

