Before the commencement of the programme, the research team will organise a 3-day training workshop for the NCM and the centre service providers, such as the administrative staff, social workers, and CWs. The training content will include the implementation process, theoretical knowledge and practical skills, documentation processes, and the referral guidelines and support system. Didactic lectures and role playing will be used to ensure that the service team members understand and are able to apply what they have learned in a case scenario. To ensure that the centre staff are competent at applying what they have learned in the programme, the NCM will use the Omaha System to conduct a comprehensive assessment, identify any problems, and provide interventions in a simulated case according to the validated protocols. In addition, the centre staff will be required to complete and pass a post-training competence test to confirm that they have mastered the knowledge required for the subjects’ recruitment procedure.

Appropriate policies and sufficient funding are important for sustaining a programme in the community. This programme will not have the capacity to change policy, but the team will capitalise on the opportunities provided in the current policy directives to work with the social service sector to promote health in the community. In recent years, the Hong Kong government has embraced the importance of primary healthcare services and has provided support and funding to non-governmental organisations to address the health and social needs of citizens.

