### Control group

Subjects in the control group will receive a monthly social telephone call from a trained research assistant. The purpose of the call will be to control the possible social effects (that is, a person will have a better social health when someone is regularly calling or caring about the person) of the intervention. When subjects have concerns about their health or have social problems, the RA will suggest that the subjects seek help from their general practitioner.

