### Outcome measures

RE-AIM [30] will be adopted as the evaluation framework of the programme. Of the five dimensions included in the RE-AIM framework, only effectiveness and maintenance outcomes will be collected from both the intervention and control groups. The outcomes of the other three dimensions—reach, adoption, and implementation—will only be collected from subjects in the intervention group.

To determine whether the programme reaches the target population, the recruitment rate and subject characteristics will be collected. The recruitment rate will be calculated by dividing the total number of subjects recruited by the total number of eligible subjects in the member list of the community centre.

Since this is a pilot study, we can only measure the effectiveness outcomes if such data can be collected. The Chinese version of the General Self-Efficacy Scale will be used to measure self-efficacy level. This scale has been validated in a Chinese population and has been shown to have good validity and reliability [36]. Version 2 of the 12-item Short Form Health Survey will be used to measure quality of life [37]. This scale measures various aspects of physical and mental health, from which physical and mental component scores will be calculated. It has been widely used, with good validity and reliability [37]. The total number of unscheduled general out-patient department, general practitioner, and emergency room visits and hospital admissions and the total number of attendances at health services will comprise the health service utilisation outcomes in this study. Health service utilisation information will be collected by the subjective reporting of the subjects and will be confirmed by examining the medical and attendance certificates. This data collection protocol has been shown to have good reliability [8].

We will explore the programme adoption by using semi-structured group interviews with the providers (i.e. the social workers and the NCMs), the involved centre staff members, and eight participants (i.e. 20% of the intervention group participants). In the interviews, the research assistant will explore the interviewee’s perceptions on the facilitating factors of and barriers to program adoption in the community centre. In addition, the research assistant will also audio-record and transcribe the conversation to examine the logistic and feasibility of the programme during the interdisciplinary care conferences.

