### Data collection

Quantitative data will be collected at baseline, before the commencement of the programme (T1); immediately post-intervention (T2); and 3 months after the completion of the intervention, to evaluate the maintenance of the programme (T3). A trained RA who is blinded to the group assignment will call the subjects to collect these data.

Three separate semi-structured interviews will be conducted at T2 to collect qualitative data from all centre staff and service providers (i.e. nurse case managers and social workers) and 20% of the intervention group subjects (i.e. 8 subjects).

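### The blinding of the T2 and T3 outcome assessor is claimed but not secured, because the same research-assistant label also covers tasks that reveal the arm; the claim for community centre staff is too broad

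*Protocol article*

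**What the plan says.** The section on study setting, subjects and recruitment introduces a trained research assistant, abbreviated RA, and then states: "The RA and the community centre staff, but not the PI or the healthcare providers, will be blinded to the group assignments". The Data collection section relies on this for the quantitative outcomes: "A trained RA who is blinded to the group assignment will call the subjects to collect these data".

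Other sections give the research-assistant role further duties:

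- Control group: "Subjects in the control group will receive a monthly social telephone call from a trained research assistant". The same paragraph then uses the abbreviation for that caller: "the RA will suggest that the subjects seek help from their general practitioner".
- Outcome measures, on the adoption interviews: "In the interviews, the research assistant will explore" the interviewees' views. The interviewees include eight intervention subjects and no controls. Data collection places these interviews at T2.
- Outcome measures, on the care conferences: "the research assistant will also audio-record and transcribe the conversation to examine the logistic and feasibility of the programme during the interdisciplinary care conferences". These conferences are monthly and are described only under Intervention group.

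For centre personnel, the Intervention group section has a community worker follow up intervention subjects under the nurse case manager's supervision. It lists those to be trained alongside the nurse as "the centre service providers, such as the administrative staff, social workers, and CWs".

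**The concern.** An assessor is blinded only if nothing else that person does reveals the arm. Calling controls, interviewing intervention subjects and recording intervention conferences each reveal it. If any of these duties falls to the person who collects T2 or T3 data, the statement of blinded assessment fails for the subjects concerned.

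The outcomes are of the kind where this matters. Self-efficacy and the SF-12 are self-reports given over the telephone. Health service use also starts from self-report, with certificates as a check. Familiarity built up over social calls in one arm, or knowledge of the programme gained in the other, could change how questions are put or answered, and differently by arm. The article plans between-group tests with p-values, and the programme is to move on to six centres, so the assessment procedure deserves to be settled in the pilot.

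The centre-staff part is a separate matter of accuracy. People who deliver part of the programme to a subject cannot be blinded to that subject's arm.

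**Working it through.** No arithmetic applies. The check traces each role through the article and asks what it reveals and when.

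**Research assistant**

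| Duty | Section | How the person is named | What the duty reveals | Timing |
|---|---|---|---|---|
| Baseline data (T1) | Study setting, subjects, and recruitment strategies | the RA | nothing | before randomisation |
| Monthly social calls | Control group | a trained research assistant, then the RA | that the subject is a control | monthly; the abstract places them with the 3-month programme, so before T2 |
| Recording care conferences | Outcome measures | the research assistant | that the subject is in the intervention arm | monthly during the programme, so before T2 |
| Interviews with eight subjects | Outcome measures; Data collection | the research assistant | that the subject is in the intervention arm | at T2, so before T3; order relative to the T2 questionnaire not given |
| Outcome data (T2, T3) | Data collection | a trained RA, described as blinded | should reveal nothing | T2 and T3 |

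Four steps follow.

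1. T1 is safe, because baseline data are complete before the principal investigator is called for the allocation.
2. The control calls reach every control. With two arms, a person who makes all of them could infer the whole allocation: a subject not on the call list is in the intervention arm.
3. The conferences could reveal the arm of any intervention subject who attends. The interviews reveal it for eight only.
4. The recruitment section blinds the RA without distinguishing one RA from another, the Control group section reuses that abbreviation for the caller, and no section says that the T2 and T3 assessor is kept apart from these duties.

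**Centre staff**

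1. The blinding statement covers the community centre staff without exception. It exempts only the principal investigator and the healthcare providers.
2. Community workers are named among the centre's service providers in the training paragraph.
3. Community workers follow up intervention subjects.
4. For these workers, the blanket statement and the assigned work cannot both hold, unless they are meant to fall under the healthcare-provider exemption. The article does not say so.

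**The case against.** **One shared RA is not stated.** A reader might infer that a single person does all these jobs and that outcome assessment is therefore unblinded. The article does not support that. The Control group and Data collection sections both use the indefinite article, and the clause describing the outcome caller as blinded can be read as picking one RA out of several. Data analysis has a research team member record and transcribe the interviews, so staff labels are used loosely. A condensed article may also leave the delegation of tasks to a fuller document. This stands as a limit on the conclusion, but it does not remove the point. The recruitment section blinds the RA as one role, and the Data analysis sentence concerns recording the interviews. It does not cover the control calls, the conferences or who conducts the interviews.

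**The interviews are a narrow route.** They involve eight subjects and ask what helped or hindered adoption. A reader might suppose that they ask subjects about benefit, but the article does not say so. This strand is therefore weaker than the control calls and the conferences.

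**Centre staff may be partly exempt.** Outcome measures and Data collection class social workers as providers, apart from centre staff, and the abstract places community workers in the health-social service team. Social workers may well fall under the exemption. For community workers the article points both ways. Being trained in the programme or interviewed about it does not by itself reveal any subject's arm, so neither is evidence against blinding. Centre staff are also not given the task of collecting the quantitative outcomes, so this strand has no direct route to assessor bias.

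**Exposure is limited.** Service use is checked against medical and attendance certificates, and the pilot measures effectiveness only if the data can be obtained. Both are fair. Neither protects the two questionnaires.

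**Conclusion.** The point holds as a claim of blinding that the assigned roles do not support as written. For the T2 and T3 self-reported outcomes, the article asserts a blinded assessor while using the same undivided label for duties that reveal the arm, and it contains nothing that separates them. For centre staff, the statement is too broad at least for community workers.

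It does not follow that assessment will be unblinded. That would require the assessor to be the person who calls controls, interviews subjects or attends conferences, and the article neither says nor excludes this. The size of any bias cannot be derived from the document, and a figure in standard-deviation units would be pure assumption, so none is given. The conclusion rests on the wording of the roles and does not depend on sample size, effect size or attrition.

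This is more than missing detail, because blinding is a stated property on which the credibility of self-reported outcomes depends. It should be corrected.

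**What to change.** 1. State that the RA who collects T2 and T3 data makes no control calls, conducts no interviews and attends no care conferences. Give those duties to other existing team members and name the roles separately.
2. Complete each subject's T2 questionnaire before any interview with that subject.
3. Limit the blinding statement for centre staff to those with no delivery or referral role, and say whether community workers and social workers count as providers or as centre staff.
4. If the roles cannot be split within the present team, withdraw the claim of blinded outcome collection and report assessment as unblinded.

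An allocation guess recorded by the assessor at T3 would be a useful optional check, but its absence is no fault.

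The cost is rewording the role descriptions and some rescheduling of team time. If separate people already fill these roles, a clarifying sentence settles the RA part.

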### Sample size

Given that this is a pilot implementation study, the sample size will follow the rule of thumb of a minimum of 30 in each group [34]. As a previous study using a health-social service partnership programme for community-dwelling older adults had an attrition rate of approximately 15% [8], we will assume a 20% drop-out rate in this study. Therefore, a sample size of 36 will be needed for each group, for a total of 72 subjects in the two groups.

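### The stated 36 per group does not retain the plan's minimum of 30 at its assumed 20% drop-out; those two inputs give 38 per group (a minor discrepancy)

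*Protocol article*

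**What the plan says.** The calculation is in the Sample size section of the protocol article and has four parts.

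- The starting point: "the sample size will follow the rule of thumb of a minimum of 30 in each group".
- The background rate: an earlier study of a similar programme in community-dwelling older adults "had an attrition rate of approximately 15" per cent.
- The rate adopted for this trial: "we will assume a 20% drop-out rate in this study".
- The result: "Therefore, a sample size of 36 will be needed for each group, for a total of 72 subjects in the two groups".

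The section on setting, subjects and recruitment fixes equal allocation: "The subjects will be randomly assigned in a 1:1 ratio to either the intervention group or control group". No formula is given for the step from 30 to 36, and no other section revisits it.

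**The concern.** The 30 is raised because subjects are expected to drop out, so it has to be read as the number that should remain afterwards. If 30 were the number to enrol, the drop-out assumption would have no job to do. On that reading the enrolled number, multiplied by the share retained, should be at least 30. It is not.

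A drop-out rate is a share of those enrolled, so the target has to be divided by the share retained. Adding 20% of the target itself gives too small a number, and 36 is exactly what that shortcut produces.

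At stake is whether the size justification does what it says. The authors chose 20% as a margin above the 15% seen before, and 36 per group does not deliver all of that margin.

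**Working it through.** **Inputs**, all from the article: minimum per group 30; assumed drop-out 20%; earlier study's attrition about 15%; stated size 36 per group, 72 in total; allocation 1:1.

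**Step 1. Reproduce the stated figure.**
- Target × (1 + drop-out): 30 × 1.20 = 36, and 2 × 36 = 72. This matches exactly.
- Target / (1 − drop-out) at the adopted 20%: 30 / 0.80 = 37.5, rounded up to 38. This does not match.
- Target / (1 − drop-out) at the earlier study's 15%: 30 / 0.85 = 35.3, rounded up to 36. This matches, but uses a rate that the article cites and then replaces.

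**Step 2. Expected completers per group = enrolled × (1 − drop-out).**

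| Enrolled per group | At 15% | At 20% |
|---|---|---|
| 36 | 30.6 | 28.8 |
| 37 | | 29.6 |
| 38 | | 30.4 |

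At 20%, 38 is the first size that reaches 30. Over two groups, 72 enrolled leave 57.6 and 76 leave 60.8, against a target of 60. Inflating the total directly gives 60 / 0.8 = 75, which cannot be split equally, so equal groups need 76.

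**Step 3. Drop-out that 36 per group can bear.** 1 − 30/36 = 0.167. So 36 retains 30 on average only if attrition is at most 16.7%.

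**Step 4. Chance of actually keeping 30.** Assume that each subject drops out independently with probability 0.20, so that completers in a group are binomial with retention 0.80. The chance for both groups is the square of the chance for one.

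| Enrolled per group | One group keeps at least 30 | Both groups do |
|---|---|---|
| 36 | 0.40 | 0.16 |
| 38 | 0.66 | 0.43 |

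The two rows belong together. Even the consistent size misses 30 in at least one group more often than not, because this kind of inflation aims at the average and guarantees no minimum.

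**The case against.** The best defence is about size. The 30 is a convention for pilot studies, not the product of a power, precision or effect-size calculation. Falling to 28.8 costs 1.2 expected completers per group. The Outcome measures section already says that effectiveness outcomes will be measured only if such data can be collected, and nothing among the Objectives turns on 29 against 30. At the one observed attrition rate in the article, about 15%, 36 per group does retain 30 on average. All of this stands, and it makes the point minor. It does not make the three statements agree.

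A second defence is that the faulty step is inferred. That also stands: 30 × 1.2 is the likely route, but 30 / 0.85 rounds up to the same 36. The discrepancy does not depend on the route, because 36 falls short of 30 at the stated 20% either way.

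A reader might infer more than the article supports:

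- *That the loss falls on the comparison three months after the programme.* Cumulative loss cannot shrink over time, so this is plausible. But the article gives no drop-out by visit and does not say at which visit the 20% applies.
- *That the error creates a 60% risk of a group ending below 30.* At 38 per group that risk is still about 34% (1 − 0.66), so much of it would remain after correction.
- *That this is the only planning number in the article.* It is not: the interview sample of eight intervention subjects is also fixed in advance.

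**Conclusion.** The point holds as an internal inconsistency of minor weight. At 20% drop-out, 36 per group leaves an expected 28.8, and the size consistent with the article's own inputs is 38 per group (76 in total). The gap is two enrolled subjects per group, or four in all.

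This rests on two things: that 30 is meant as the number remaining, which the inflation implies, and that the 20% is a share of those enrolled, which is the ordinary meaning of a drop-out rate. The probabilities also assume independent drop-out; the expected numbers do not.

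It would be wrong to conclude that the trial is underpowered or its design unsound. The article makes no power claim, and no error rate or objective depends on the difference between 29 and 30 completers.

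**What to change.** Correct the last step of the Sample size section in one of two ways.

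1. **Keep 36 per group (72 in total) and restate what it delivers.** For example: 36 per group retains 30 per group provided attrition does not exceed 16.7%; at the earlier study's rate of about 15%, about 30.6 per group would remain, and at 20% about 29. This costs one sentence and no extra subjects. The price is openness: the tolerance shown is narrower than the 20% now claimed.
2. **Keep both 20% drop-out and 30 completers, and state 38 per group (76 in total).** This costs four more subjects and an update wherever 72 appears. The interview sample need not change: 20% of 38 is 7.6, which still rounds to eight.

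Either is acceptable. The second is the one that follows from the inputs as written; the first accepts a lower tolerance in exchange for leaving recruitment alone. Whichever is chosen, show the formula, so that the step can be checked and is not carried unexamined into the planned extension to six centres. If retention probabilities are quoted, give them for both sizes.

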### Ethical considerations

Ethical approval has been granted by the Departmental Research Committee (Department of Nursing) on behalf of the PolyU Institutional Review Board (ref. HSEARS20201130001) of Hong Kong Polytechnic University. Information about the study’s significance, purpose, procedures, risks, and benefits will be provided to all eligible subjects. Subjects will be reassured that they can refuse participation and withdraw from the study anytime without penalty. Subjects will sign a consent form after they have expressed their understanding of the study. A telephone hotline will also be provided for subjects to ask questions about the study.

